### Study Design and Sample Size

This study uses a mixed methods (qualitative-quantitative convergent) design involving a nonrandomized 2-arm trial comparing the 6-month P2P intervention group with a 1:2 matched comparison group.

As this study is a pilot intervention, sample sizes were determined by what was deemed feasible within the available time frame and resources rather than power calculations. We aimed to recruit 35 veterans with HNHR or referred veterans for participation in the P2P intervention.

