#### Quantitative Analysis

For our primary outcome, we will first calculate the difference in the number of primary care PACT outpatient encounters 6 months before and after enrollment for each participant in both intervention and comparison groups. An independent, 2-tailed, 2-sample *t* test will then be used to compare the means of the pre-post differences in the number of outpatient PACT encounters between intervention and comparison groups. The mean pre-post difference will be reported for each group with the corresponding SDs and 95% CIs. The folded F statistics will be evaluated to report either the pooled or Satterthwaite *P* value. We will calculate group-specific means and proportions for sociodemographic and clinical factors. At baseline, categorical variables will be compared between groups with the Pearson chi-square test or with the Fisher exact test for rare outcomes. The *t* test will be used to compare means across groups. *P* values will be reported, with lower values interpreted as more stable and less likely to be sporadic. All quantitative analyses will be performed using SAS 9.4 (SAS Institute Inc).

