## Results

The P2P project was funded in October 2019. Study enrollment began in July 2020 and was completed in March 2022. Our sample size consists of 114 veterans: 38 (33.3%) P2P intervention participants and 76 (66.7%) matched comparison group participants. Data analysis is underway, and study findings are expected to be published in late 2023.

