### Limitations

As this is a nonrandomized study, the greatest challenge is the identification of an appropriate comparison group. We selected a matched comparison group from the same HNHR list from which the intervention participants were recruited to reduce selection bias. By selecting a matched comparison group that is similar according to a set of matching variables, we help to ensure that any observed differences in outcomes between the intervention and comparison groups can be more confidently attributed to the treatment itself, rather than other factors that may differ between the groups. The final sample size included 114 veterans: 38 (33.3%) P2P intervention participants and 76 (66.7%) matched comparison group participants. We made efforts to mitigate sample size limitations by including a 1:2 ratio of comparison group participants. In addition, the inclusion of referred patients may be deemed a deviation from the original protocol. However, the referred veterans will be assessed for comparable characteristics with veterans recruited from the HNHR list. Recent VA data demonstrate that using a combination of administrative data such as the HNHR list and clinician judgment is best suited for identifying patients for intensive care management interventions [54].

Safety precautions during the COVID-19 pandemic and home visits presented a potential risk for the intervention in terms of protection of the peers and the protection of older veterans with HNHR who are frail. The peers were trained by the home-based primary care team to make home visits and were trained on proper personal protective equipment use. Furthermore, peer use of remote care was limited by the access to, and willingness and ability to use, technology of the veteran with HNHR [55]. Peers used remote care where suitable. This aligns well with national VA priorities and stakeholder feedback.

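### Baseline P values at 38 versus 76 are a weak check on balance, and any imbalance passes straight into an unadjusted primary t test

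*Protocol article*

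**What the plan says.** The Protocol article (Study Design and Sample Size) describes a "nonrandomized 2-arm trial comparing the 6-month P2P intervention group with a 1:2 matched comparison group", with "sample sizes were determined by what was deemed feasible within the available time frame and resources rather than power calculations". The Results section gives the achieved sample as "38 (33.3%) P2P intervention participants and 76 (66.7%) matched comparison group participants".

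Under Quantitative Analysis, group means and proportions are to be calculated for sociodemographic and clinical factors. The formal comparison is then by test: "At baseline, categorical variables will be compared between groups with the Pearson chi-square test or with the Fisher exact test for rare outcomes", and for continuous variables, "The *t* test will be used to compare means across groups". No significance level is set. P "values will be reported, with lower values interpreted as more stable and less likely to be sporadic".

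The primary analysis, in the same section, is an independent two-sample t test on each veteran's change in PACT outpatient encounters from the 6 months before to the 6 months after enrollment. No covariate is named. Under Matched Comparison Group, the matching variables are age, CAN score, JEN Frailty Index and Nosos score. The pre-enrollment encounter count is not among them.

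The Limitations section says that "the referred veterans will be assessed for comparable characteristics with veterans recruited from the HNHR list", without naming a method or a criterion.

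**The concern.** In a nonrandomized comparison, the baseline table has to show how far apart the groups are. A P value mixes the size of a difference with the size of the sample. At 38 versus 76, a difference large enough to matter can give an unremarkable P value.

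Imbalance is plausible here. Intervention veterans were called, mailed or referred and then agreed to take part, and some were not on the HNHR list. Comparators were drawn from that list. Prior PACT use, the baseline of the primary outcome, was not matched.

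The primary estimate is unadjusted, so an imbalance on anything that predicts the change in encounters enters it directly. At stake is how much of an observed group difference can be credited to the intervention.

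**Working it through.** **Inputs.** n1 = 38 and n2 = 76 (Results), so N = 114 and df = 112; the 1:2 ratio and the percentages agree. The article states no alpha, power or detectable difference, so it has no figure to reproduce. Alpha is assumed two-sided at 0.05, with 0.10 and 0.01 as the range. The groups are treated as independent samples, as the plan's own tests treat them. The figures therefore describe unmatched variables best.

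**Smallest observed difference that reaches significance**

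SE of a standardized difference = sqrt(1/38 + 1/76) = 0.1987. The cut-off is t(1 − alpha/2, 112) × SE:

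- alpha 0.10: 1.659 × 0.1987 = 0.33 SD
- alpha 0.05: 1.981 × 0.1987 = 0.394 SD
- alpha 0.01: 2.620 × 0.1987 = 0.52 SD

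At these sample sizes, an observed 0.25 SD gives P = 0.21 and an observed 0.30 SD gives P = 0.13.

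**Chance of flagging a true imbalance** (noncentral t, alpha 0.05)

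| True imbalance (SD) | Flagged | Missed |
|---|---|---|
| 0.10 | 8% | 92% |
| 0.20 | 17% | 83% |
| 0.30 | 32% | 68% |
| 0.39 | 49% | 51% |
| 0.50 | 70% | 30% |

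A flag with 80% probability needs a true imbalance of about 0.56 SD.

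**Categorical variables** (uncorrected Pearson chi-square, alpha 0.05). With 23/76 (30%) in the comparison group, the intervention group must reach 19/38 (50%), a gap of about 20 points, to be significant. From 50% the gap needed is about 21 points; from 10.5% it is about 16 points.

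**Effect on the primary estimate.** Take a covariate with standardized imbalance SMD and correlation r with the change score.

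- Bias in SD units of the change = SMD × r.
- Shift of the test statistic = bias / 0.1987.
- False-positive rate ≈ P(|Z + shift| > 1.96).

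With SMD = 0.3:

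| r (assumed) | Bias (SD) | Shift | False-positive rate |
|---|---|---|---|
| 0.1 | 0.03 | 0.15 | about 5.3% |
| 0.3 | 0.09 | 0.45 | about 7.4% |
| 0.5 | 0.15 | 0.75 | about 12% |

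The article gives no value for r. The top of the range is conceivable for the pre-enrollment count. If pre and post counts have equal SDs and correlation rho, the count correlates with the change at −sqrt((1 − rho)/2), which is −0.5 at rho = 0.5. That creates bias only if both groups regress toward a common mean, which is a further assumption.

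**Referred versus list-recruited veterans.** The split of the 38 is not stated. For assumed splits from 10/28 to 19/19, SE runs from sqrt(1/10 + 1/28) = 0.368 to sqrt(2/19) = 0.324. With t(0.975, 36) = 2.028, the cut-off runs from 0.75 down to 0.66 SD. This applies only if a test were used; the article names none.

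**A selection trigger at |SMD| > 0.1.** For a perfectly balanced unmatched variable, P(|Z| > 0.1/0.1987) = P(|Z| > 0.50) ≈ 61%. Such a trigger would mostly select noise.

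**The case against.** The strongest reply is that the article contains no rule turning a nonsignificant baseline test into a declaration of balance. It sets no alpha and describes P values as read on a gradient. It also tabulates means and proportions, so a 30% versus 50% difference would be visible whatever its P value. The Limitations section rests attribution on the matching, in hedged terms, and calls finding a comparison group the greatest challenge. All of this stands. A reader might infer that the plan will declare confounding absent when tests are nonsignificant; the text does not support that.

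Three further points also stand:

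- The 0.39 SD figure is a cut-off for observed differences. A true imbalance of that size is flagged about half the time, so it would be wrong to say that the tests cannot see it.
- The 12% false-positive figure needs r = 0.5. The outcome is a change score, so stable differences in level between veterans cancel, and at r = 0.1 the inflation is negligible.
- This is a pilot of preliminary effect reported in a condensed article. A fuller analysis plan may already provide balance measures or adjusted analyses.

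The last point does not remove the concern. The baseline method and the unadjusted primary test are choices the article states, and both bear on bias.

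**Conclusion.** The concern holds in a limited form. Baseline comparison in this nonrandomized study relies on significance tests beside raw means and proportions, and the primary t test is unadjusted. At an assumed two-sided 0.05, observed differences below about 0.39 SD are nonsignificant (0.33 to 0.52 SD for alpha 0.10 to 0.01). A true 0.3 SD imbalance is missed about 68% of the time, so a nonsignificant P value is not evidence of balance.

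For a 0.3 SD imbalance, the effect on the primary test runs from negligible (about 5% false positives at r = 0.1) to material (about 12% at r = 0.5). Both the imbalance and the correlations are assumptions. The documents do not show that an imbalance exists, nor that the authors would treat nonsignificance as proof of comparability. The change is worth making before results are read, since the article says analysis is underway.

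**What to change.** 1. Report standardized mean differences for the variables collected in both groups, in place of or beside the baseline P values. Include the four matching variables and the 6-month pre-enrollment PACT encounter count. Table 3 marks demographics, clinical scores and health care use as collected in both groups.
2. Give the same descriptive comparison for referred versus list-recruited veterans.
3. Beside the t test, report an estimate adjusted for a fixed set named in advance: age, CAN score, JEN Frailty Index, Nosos score and the pre-enrollment PACT count. Do not select covariates by an observed |SMD| above 0.1.

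**Cost.** One extra table column and no new data. Five covariates reduce the residual degrees of freedom from 112 to 107. The change-score estimate and the estimate adjusted for the baseline count can differ in a nonrandomized design, because they make different assumptions about how the groups would have evolved without the intervention. Both should be shown, and any disagreement reported as uncertainty about the effect.

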#### Qualitative Analysis

Qualitative data analysis will follow a structured rapid approach using deductive coding as well as the Consolidated Framework for Implementation Research (CFIR) [52]. A mixture of detailed note-taking and audio-recorded semistructured interviews will be used. Interviews will be transcribed and deidentified. Researchers will enter transcripts into NVivo 12 (QSR International), a software program used for qualitative and mixed methods research, and begin by reading each transcript repeatedly from beginning to end. To facilitate qualitative data coding and organization, we will use an NVivo project template, prepopulated with CFIR construct codes. Codes selected a priori include constructs within the following domains: outer setting, inner setting, and implementation process. Although constructs are selected a priori, we will allow for the expansion of codes and emergent themes as necessary.

To enhance validity and reliability of the qualitative data analysis, we will conduct exercise debriefings within the study team to evaluate potential differences in coding across analysts and resolve coding differences as needed. Running documents of all coding decisions, processes, and analyses will be kept, ensuring proper data management and coding practices.

### Ethics Approval, Participation, and Privacy Considerations

This study was approved by the Miami VA Healthcare System institutional review board (#1592752). No compensation was provided to veterans for participation. A waiver of Health Insurance Portability and Accountability Act (HIPAA) authorization was granted based on the determination that the risk to the privacy of individuals is minimal. To ensure privacy, efforts were taken to protect the identity of participants and ensure that data were kept confidential. Names, addresses, and social security numbers were replaced with a unique code and will only be maintained on a VA server; documentation of the procedure used to code the data will remain within the VA. All identifiers collected as part of this research project will be destroyed as per the records control schedule (RCS 10-1) of the Veterans Health Administration (VHA). Electronic files will be stored in folders with restricted access on a protected computer shared drive behind the VA firewall in a secure server. Nonelectronic records will be maintained in locked cabinets and behind locked doors. Information will be located in an area with limited public access. Data will not be transmitted as an attachment to unprotected email messages. The data will be accessible only to personnel involved in the study. All staff will be trained to avoid breach of confidentiality issues.

## Results

The P2P project was funded in October 2019. Study enrollment began in July 2020 and was completed in March 2022. Our sample size consists of 114 veterans: 38 (33.3%) P2P intervention participants and 76 (66.7%) matched comparison group participants. Data analysis is underway, and study findings are expected to be published in late 2023.

## Discussion

### Overview

Peers are increasingly being deployed in a variety of health care settings to provide patient-centered care. At the VA, efforts are underway to integrate peers in primary care settings. The role of peers is expanding and evolving, and peers are currently being proposed to be added in primary care PACTS at all VA facilities [53]. The use of peers in primary care settings at the VA is still relatively new, and innovative models for the use of peers are being developed at several VA sites based on local needs.

The P2P intervention aims to address unmet needs of older veterans with HNHR who are frail by addressing individual health and social needs as well as the home environment. Although peers are not medical providers, they are well suited to assess and understand patients’ perspectives and needs and are empowered to recommend patient-centric strategies to address them. This intervention aims to improve patient health care engagement through the timely use of needed services and supports. The protocol presented has undergone multiple modifications using feedback from peers, the PACT, stakeholders, and veterans. This study originally aimed to test the integrated P2P intervention using a structured 6-month experimental design. However, veterans with HNHR are a population with complex needs and with multimorbidities and poor health care engagement. They are challenging to treat because they often have more immediate health and living concerns that make participating in long interventions a last priority. Taking these challenges into consideration, a more flexible intervention schedule was developed in response to feedback from veterans with HNHR regarding their concerns with the intervention duration and time commitment required. In practice, the educational components are not constrained to specific weeks within the 6 months; instead, peers have flexibility on deciding when to cover topics within the allotted time frame. This flexibility takes into consideration the heterogeneity and complex needs of this population.

During the design phase, we used several strategies to improve recruitment: reducing the number of data collection instruments to reduce respondent burden, allowing peers to use their peer style to gather data while maintaining trust with the veteran, increasing provider knowledge of referrals to the P2P intervention, accepting patients referred by PACT providers, mailing recruitment letters, and giving peers flexibility to adapt the intervention to make it more veteran-centric as needed.

Peers are currently delivering the P2P intervention, conducting home visits, and identifying unmet needs as part of their routine clinical duties at the Miami VA Healthcare System. Because of the limitations with enrolling participants owing to COVID-19–related delays and the complexity of veterans with HNHR, we obtained permission to use clinical data from all veterans who participated in the P2P intervention. Our ability to track health care use and collect demographic and clinical data from electronic medical records presents us with the opportunity to assess the efficacy of the P2P intervention with data that are not easily collected via questionnaires. The results from this study will aid our understanding of the acceptability and feasibility of the P2P intervention and its effect on health-related outcomes.

### Strengths

The P2P intervention has several strengths. First, its novel approach of using peers in the PACT beyond the VA and into the home allows peers to serve as *eyes in the home* and identify needs that otherwise may continue to go unmet without proper care coordination. Second, using the AFHS and a whole health approach allows the peers and veterans to develop a personalized health plan based on individual values, needs, and goals. Third and last, prior VA research notes the need for functional and cognitive status as well as data related to social determinants of health to be a part of the routine electronic health record [54]. The needs identification tool we developed for this intervention was converted into a CPRS template with the goal of harmonizing data and coordinating care with the PACT on veterans’ unmet health and social needs.

### Limitations

As this is a nonrandomized study, the greatest challenge is the identification of an appropriate comparison group. We selected a matched comparison group from the same HNHR list from which the intervention participants were recruited to reduce selection bias. By selecting a matched comparison group that is similar according to a set of matching variables, we help to ensure that any observed differences in outcomes between the intervention and comparison groups can be more confidently attributed to the treatment itself, rather than other factors that may differ between the groups. The final sample size included 114 veterans: 38 (33.3%) P2P intervention participants and 76 (66.7%) matched comparison group participants. We made efforts to mitigate sample size limitations by including a 1:2 ratio of comparison group participants. In addition, the inclusion of referred patients may be deemed a deviation from the original protocol. However, the referred veterans will be assessed for comparable characteristics with veterans recruited from the HNHR list. Recent VA data demonstrate that using a combination of administrative data such as the HNHR list and clinician judgment is best suited for identifying patients for intensive care management interventions [54].

Safety precautions during the COVID-19 pandemic and home visits presented a potential risk for the intervention in terms of protection of the peers and the protection of older veterans with HNHR who are frail. The peers were trained by the home-based primary care team to make home visits and were trained on proper personal protective equipment use. Furthermore, peer use of remote care was limited by the access to, and willingness and ability to use, technology of the veteran with HNHR [55]. Peers used remote care where suitable. This aligns well with national VA priorities and stakeholder feedback.

### Conclusions

Peers may help bridge the gap between PACT providers and veterans with HNHR by evaluating veterans’ needs outside of the clinic, summarizing identified problems, and developing team-based solutions in partnership with the PACT. The home visit component of the intervention provides *eyes in the home* and may be a promising and innovative tool to identify unmet needs and home safety risks. The focus of our design emphasizes a community-based approach to successfully identify unmet needs and link individuals with HNHR with needed and effective health care services.

This project is timely because the *Veteran Peer Specialist Act of 2021* (Bill HR 4575) was recently approved by Congress to expand the peers-in-the-PACT program to all VA sites. The P2P intervention offers a protocol for integrating peers into the PACT that enhances and adds to the services provided by peers at the VA. The P2P intervention is being tested under real-world conditions using certified VA peer support specialists selected through usual VA hiring practices and assigned to the VA primary care service. The results collected from this study will provide important information on the effectiveness of a peer-led home visit intervention for veterans with HNHR who are considered vulnerable as an innovative strategy to identify need gaps using the AFHS 4Ms framework and coordinate care to increase timely access to needed services. Our findings will further gauge the feasibility of this framework in the existing health care system using peers. This intervention may highlight the innovative role that peers in the PACT may play to extend the reach of the PACT into the veterans’ homes to implement evidence-based long-term services and supports proactively and more equitably. Timely access to needed long-term care services and supports as a *preventive* measure may help meet veterans’ preference to age in place.

## Abbreviations

4Ms: mobility, mind, medications, and matters most
5Ms: mobility, mind, medications, matters most, and multicomplexity
AFHS: age-friendly health system
CFIR: Consolidated Framework for Implementation Research
CPRS: computerized patient record system
GEC: Geriatric and Extended Care
GECDAC: Geriatric and Extended Care Data Analysis Center
HIPAA: Health Insurance Portability and Accountability Act
HNHR: high needs and high risk
LTIC: long-term institutional care
MISSION: Maintaining Internal Systems and Strengthening Integrated Outside Networks
P2P: peer-to–patient-aligned care team
PACT: patient-aligned care team
RE-AIM: reach, effectiveness, adoption, implementation, and maintenance
VA: Department of Veterans Affairs
VHA: Veterans Health Administration
